3.9 Extracurricular Physical Activity, Diet, and Sleep

Extracurricular physical activity is monitored using the "Physical Activity Questionnaire for Children and Adolescents (PAQ)." Sleep is assessed using the "Pittsburgh Sleep Quality Index." Diet is monitored using the "Dietary Behavior Scale."

3.10 Data Statistics and Analysis

Data will be analyzed using SPSS 26.0. Normality tests will be performed using the Shapiro-Wilk method, and data will be presented as mean ± standard deviation. Paired sample t-tests will be used to compare differences before and after intervention for each indicator. Independent sample t-tests will be used to compare baseline indicators between the two groups and differences between the pre- and post-intervention values. Statistical significance is set at P<0.05.

1. **Expected Timeline and Completion Dates**

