**2. Research Objective**

This study will use the China Health and Physical Education Curriculum Model for 12 weeks of physical education teaching. Relevant physical health and psychological health indicators will be tested before and after the teaching. Changes in metabolites before and after the teaching will be detected through non-targeted metabolomics technology. The study will analyze the effects and metabolic mechanisms of one-time and long-term teaching using the China Health and Physical Education Curriculum Model on improving students' physical and mental health levels, aiming to provide new insights into improving students' physical and mental health through this model.

1. **Research Methodology**

- 1. Participants and Grouping

The sample size was calculated using G*Power software, selecting “Means: Difference between two independent means (two groups)” under “t tests.” The assumptions included a medium effect size of 0.5, an α error probability of 0.05, and a power (1 - β error probability) of 0.80, with equal sample sizes in both groups. The minimum required sample size for the study was calculated to be 64.

This study employed a randomized controlled trial design. Six classes of the same grade were randomly selected, with three assigned to the experimental group and the other three to the control group. The researchers wrote the allocation information for each participating class (e.g., experimental or control group) on slips of paper and placed these slips into envelopes. Each envelope contained the random allocation information for the respective class. Both the participants and their parents in the two groups were introduced to the content of the experiment and the precautions during the experimental process to ensure they had a detailed understanding. After obtaining the opinions of the student participants and their parents based on the inclusion and exclusion criteria, informed consent forms were signed.

3.2 Inclusion Criteria, Exclusion Criteria, Criteria for Removal, and Mid-study Withdrawal Criteria

Inclusion criteria: (1) Primary and secondary school students; (2) Able to complete the 12-week intervention and the three tests before the intervention, after the first intervention, and after 12 weeks of intervention.

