Exclusion criteria: (1) Students with contraindications to physical activity; (2) Students with severe cardiovascular or musculoskeletal diseases; (3) Students who are sick, injured, have chronic diseases, are taking medication, or are in their menstrual period (female students); (4) Students who have not signed the informed consent form.

Criteria for removal: (1) Students absent for more than one-third of the sessions; (2) Students who are unable to complete the tests due to personal or family reasons; (3) Students who participated in other sports training sessions during the intervention, violating the intervention plan.

Mid-study withdrawal criteria: Students who transferred schools or could not continue participating in the study due to other reasons.

3.3Experiment Content

This study was primarily conducted in primary and secondary schools, involving six classes (approximately 300 students) who voluntarily participated. Three classes were designated as experimental groups, which adopted the Healthy Physical Education Curriculum Model of China for physical education instruction, while the other three classes served as control groups, receiving traditional physical education instruction.

The experimental groups underwent 12 weeks of physical education instruction based on the Healthy Physical Education Curriculum Model of China, whereas the control groups followed the conventional traditional physical education instruction for the same duration. Pre- and post-instruction assessments were conducted to measure the students' physical and mental health indicators. The physical health indicators were evaluated according to the National Student Physical Health Standard (Revised in 2014), which included anthropometric measurements, vital capacity, speed, strength, flexibility, agility, and other indicators. The mental health indicators were assessed through questionnaires, covering healthy behaviors, sportsmanship, depressive symptoms, and other indicators. Additionally, 40 students (20 from the experimental group and 20 from the control group) were randomly selected to provide 15 ml of urine samples before instruction, after the first session of instruction, and after 12 weeks of instruction. Non-targeted metabolomics techniques were employed to detect changes in metabolites within the body, in order to explore the underlying mechanisms by which exercise promotes health.

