3.5 Experimental Procedure

Informing the research process and precautions—Grouping by class—Pre-instruction testing (including physical health indicators, mental health indicators, and metabolite collection)—Testing after the first session of instruction (metabolite collection only)—Conducting 12 weeks of physical education instruction (experimental groups adopting the Chinese Healthy Physical Education Curriculum Model, control groups adopting traditional physical education instruction)—Post-instruction testing (consistent with pre-instruction testing).

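### Whole classes are allocated (3 vs 3), but section 3.10 compares the arms on physical and psychological change with a t-test that treats students as independent

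*Protocol*

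**What the plan says.** Allocation is by class. Under Research Methodology, Participants and Grouping, the protocol says: "Six classes of the same grade were randomly selected, with three assigned to the experimental group and the other three to the control group". On the envelopes it adds: "Each envelope contained the random allocation information for the respective class". Section 3.5 lists the step as "Grouping by class". Section 3.3 gives the size: "involving six classes (approximately 300 students) who voluntarily participated".

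The analysis in section 3.10 is by student: "Independent sample t-tests will be used to compare baseline indicators between the two groups and differences between the pre- and post-intervention values", with the threshold "Statistical significance is set at P<0.05". I read the second half of the first sentence as a between-arm comparison of change scores. It is the only between-arm outcome test named for the physical and psychological indicators.

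The sample size rests on the same assumption. It uses the G*Power t-test for two independent means, with "a medium effect size of 0.5", alpha 0.05 and power 0.80, and reaches 64. No section mentions an ICC, a design effect, a class term or an analysis of class summaries.

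**The concern.** An independent-samples t-test takes its standard error from the spread between students, as if each had been allocated separately. Here there are six allocated units. The curriculum is delivered to whole classes over 36 lessons, and Table 1 defines it partly by teaching method and classroom atmosphere, which act on the class as a whole. Changes within a class can therefore be expected to correlate, and an ICC of zero cannot be assumed.

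With three classes per arm, chance differences between classes do not average out. The planned test reads them as a treatment effect. The risk is a false claim for the curriculum on any of the physical or psychological indicators, at a rate above the stated 5%.

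**Working it through.** **Inputs from the protocol.** Six classes, 3 vs 3 (Participants and Grouping); about 300 students (section 3.3), so 300/6 = 50 per class and 150 per arm; significance level 0.05 (section 3.10); effect size 0.5, power 0.80 and equal groups (Participants and Grouping).

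**Assumed.** The ICC of the pre-post differences (not given; range 0.005 to 0.10), equal class sizes, and normally distributed outcomes.

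**1. The protocol's own figure.** Exact noncentral-t power for two independent means, d = 0.5, two-sided 0.05: 64 students per arm (128 in total) gives power 0.801. A one-sided test would need 51 per arm. The stated 64 therefore reproduces as a two-sided, per-arm count of independent students. This shows that the student is the planned unit of analysis. (The protocol words 64 as the minimum for the study. That is a separate matter, and about 300 students exceeds either reading.)

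**2. Type I error of the planned test.** Design effect DE = 1 + (m - 1) × ICC. True error ≈ 2 × [1 - Φ(1.96/√DE)]. For example, at m = 50 and ICC 0.05: DE = 1 + 49 × 0.05 = 3.45; 1.96/√3.45 = 1.055; error = 0.291. The simulated column uses 100,000 trials of 3 vs 3 classes per row. Effective n per arm is 150/DE.

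| ICC | DE (m = 50) | Error, formula | Error, simulated | Effective n per arm |
|---|---|---|---|---|
| 0 | 1.00 | 0.050 | 0.049 | 150 |
| 0.005 | 1.25 | 0.079 | 0.080 | 120.5 |
| 0.01 | 1.49 | 0.108 | 0.109 | 100.7 |
| 0.05 | 3.45 | 0.291 | 0.295 | 43.5 |
| 0.10 | 5.90 | 0.420 | 0.426 | 25.4 |

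At ICC 0.05 and 0.10 the effective sample per arm is below the protocol's own 64.

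**3. Fewer students analysed per class.** Section 3.2 lists exclusion and removal criteria, so 50 per class is an upper guide. With 21 per class (126 in total, close to the 128 of step 1), DE is 1.20, 2.00 and 3.00 at ICC 0.01, 0.05 and 0.10. The simulated error is 0.074, 0.169 and 0.264.

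**4. Class-level test.** A t-test on six class means has 4 df and a critical value of 2.776. Its simulated type I error at m = 50 is 0.049 to 0.051. For power, take d in units of the total SD of the change score. The variance of a class mean is V = ICC + (1 - ICC)/50, and the noncentrality is 0.5/√(2V/3).

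| ICC | V | Noncentrality | Power |
|---|---|---|---|
| 0.01 | 0.0298 | 3.55 | 0.755 |
| 0.05 | 0.0690 | 2.33 | 0.429 |
| 0.10 | 0.1180 | 1.78 | 0.279 |

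Power is 0.823 at ICC 0.005, so the stated 0.80 is lost somewhere between 0.005 and 0.01. At 50 students per class, reaching 80% takes 4, 6 or 9 classes per arm at ICC 0.01, 0.05 or 0.10.

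**5. Permutation test.** Six classes split 3 vs 3 in C(6,3) = 20 ways, so the smallest two-sided p is 2/20 = 0.10.

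**The case against.** **A statistical analysis plan may exist and handle this.** It might add a class term. But section 3.10 names the test, and the sample size uses the same independence assumption. This is a stated analysis that does not match the design, not a detail left open.

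**The inflation is not a documented fact.** This stands. A reader might infer that the error rate is certainly several times 5%. The protocol gives no ICC for change scores. At 0.01 the error about doubles, at 0.005 it is 8%, and near zero the problem vanishes. It is also smaller with fewer students analysed per class.

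**The reasons for correlation go beyond the text.** This stands in part. The protocol does not say how teachers are assigned to classes or how test sessions are organised, so a shared teacher or shared test conditions would be inference. Delivery of the teaching to whole classes is stated, and that is enough to rule out assuming independence.

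**The metabolite results are not affected in the same way.** This stands. A reader might extend the point to every outcome. Section 3.8 describes before-after comparisons screened by within-group t-tests and names no between-arm metabolite test. If one were run on the 20 vs 20 subsample, with about 7 students per class if spread evenly, the error would be about 6%, 9% and 12% at ICC 0.01, 0.05 and 0.10.

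**Confidence intervals.** One might add that the intervals will be too narrow. Section 3.10 plans none, only means with standard deviations and p-values, so that claim has nothing to attach to.

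**Conclusion.** The point holds for the between-arm comparisons of physical and psychological change. The mismatch between class allocation and a student-level test is in the text and does not depend on any assumed figure. The size of the error does: about 11%, 29% or 42-43% against a nominal 5% at ICC 0.01, 0.05 or 0.10 with about 50 students per class, and about 7%, 17% or 26% with 21. These figures assume equal class sizes and normal outcomes.

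It must be fixed, because it affects the trial's main causal comparison and raises the rate of false claims. The 80% power rests on the same independence assumption and does not survive the correction at ICC 0.01 or above.

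**What to change.** In section 3.10, replace the between-group independent t-test on pre-post differences with one of the following, named in advance:

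- a t-test on the six class means of the pre-post differences, 3 vs 3, on 4 df; or
- a linear mixed model (SPSS MIXED) with the student's baseline value as a covariate, a random class intercept, and Satterthwaite or Kenward-Roger degrees of freedom.

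The first is the simpler and safer choice. With six classes the model's class variance may be estimated at zero, and it then falls back towards the student-level test. If class means are adjusted for a class-level baseline covariate instead, 3 df remain, not 4. Report the ICC for each indicator. Do not rely on a class-level permutation test at 0.05, since it cannot go below p = 0.10.

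Under Participants and Grouping, restate the power with the class as the unit, over a stated range of ICCs.

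**Cost.** The analysis change needs new wording and modest extra work in the same software, with no new data. The real cost is power: about 0.76, 0.43 and 0.28 at ICC 0.01, 0.05 and 0.10, against the stated 0.80. Only more classes would recover it. If the number of classes can no longer change, the report should say that the trial may miss an effect of 0.5.

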Furthermore, during the instructional period, all students in both groups were required to wear Polar heart rate monitors to track their exercise heart rates. Questionnaires were also used to assess extracurricular physical activity, diet, and sleep patterns, in order to eliminate metabolic interferences resulting from other factors.

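### Section 3.10 compares the arms on raw pre-post change although every indicator's baseline is collected; adjusting for the pupil's own baseline would usually be more precise and would handle chance imbalance better.

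*Protocol*

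**What the plan says.** Section 3.10 fixes the comparison of the indicators in three steps.

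- Within each group: "Paired sample t-tests will be used to compare differences before and after intervention for each indicator".
- Between groups: independent-sample t-tests to "compare baseline indicators between the two groups and differences between the pre- and post-intervention values". The natural reading is one t-test on baseline values and one on the change from before to after.
- Threshold: "Statistical significance is set at P<0.05".

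No baseline covariate, regression model or class term appears in the document. The baseline is nevertheless available. Section 3.3 has the physical and mental indicators assessed before and after instruction, and section 3.5 makes the final testing the same as the first. Sex must be known, because section 3.6 assigns different tests to girls and boys. Allocation is by class, three per arm, with about 300 pupils (Participants and Grouping; section 3.3).

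**The concern.** A change score subtracts the whole baseline, which amounts to fixing the baseline coefficient at 1. When the pre-post correlation is below 1 and the SDs are similar, the right coefficient is smaller. The change score then carries noise that adjustment would remove. If the arms happen to start apart, it also over-corrects: the arm that starts higher is expected to fall back towards the mean, and this is counted against it.

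With three classes per arm, a noticeable chance difference at baseline is likely. The planned baseline t-test does not help. It corrects nothing, section 3.10 attaches no decision to it, and a non-significant result would not show balance. At stake are precision and the credibility of the estimate in the one allocation the trial will have.

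**Working it through.** **Inputs from the protocol.** Effect size 0.5, alpha 0.05, power 0.80, equal groups, stated size 64 (Participants and Grouping); 3 classes per arm (same place); about 300 pupils, so about 50 per class and 150 per arm (section 3.3). **Assumed, because the protocol gives neither:** pre-post correlation rho from 0.3 to 0.9, and intraclass correlation (ICC) from 0 to 0.10.

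**1. The plan's own figure.** It rests on a "medium effect size of 0.5, an α error probability of 0.05, and a power (1 - β error probability) of 0.80, with equal sample sizes". A two-sided two-sample t-test needs 64 per arm (128 in total, power 0.801); one-sided it needs 51 per arm. So 64 reproduces as a two-sided figure per arm. The calculation has no baseline term.

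**2. Precision.** Set the pre and post SDs to 1.

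- Change score: variance per pupil = 1 + 1 - 2rho = 2(1-rho).
- Baseline-adjusted: variance per pupil = 1 - rho².
- Ratio = (1-rho)(1+rho) / [2(1-rho)] = (1+rho)/2.

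| rho | Change | Adjusted | Ratio | n per arm, change vs adjusted | Power at 64 per arm, change vs adjusted |
|---|---|---|---|---|---|
| 0.3 | 1.40 | 0.91 | 0.65 | 88 vs 58 | 0.667 vs 0.843 |
| 0.5 | 1.00 | 0.75 | 0.75 | 63 vs 48 | 0.807 vs 0.904 |
| 0.7 | 0.60 | 0.51 | 0.85 | 38 vs 33 | 0.955 vs 0.977 |
| 0.9 | 0.20 | 0.19 | 0.95 | 13 vs 12 | about 1.00 for both |

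The last two columns use the normal approximation, take 0.5 on the week-12 SD scale and ignore clustering. They compare the two methods and do not give this trial's real power. Below rho = 0.5 the change score (variance above 1) is less precise than the week-12 value alone (variance 1).

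**3. Chance imbalance.** Var(D) = 2[ICC/3 + (1-ICC)/150] = 2(1 + 49 × ICC)/150.

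- ICC 0: sqrt(2/150) = 0.12 SD
- ICC 0.02: sqrt(2 × 1.98/150) = 0.16 SD
- ICC 0.05: sqrt(2 × 3.45/150) = 0.21 SD
- ICC 0.10: sqrt(2 × 5.90/150) = 0.28 SD

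Given D, the change score is off by rho × D - D = -(1-rho)D. For D = 0.214 SD this is 0.107 SD at rho 0.5, 0.064 at 0.7 and 0.021 at 0.9. Against the design effect of 0.5 these are 21%, 13% and 4%. A simulation of six classes of 50 with one rho at both levels gave slopes of the error on D of -0.50, -0.30 and -0.10 for the change score at rho 0.5, 0.7 and 0.9, and about 0 after adjustment.

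**4. Baseline test.** A pupil-level t-test is significant by chance with probability 2[1 - Φ(1.96 × 0.115/SD of D)]: 5% at ICC 0, 29% at 0.05 and 42% at 0.10. The excess over 5% comes from ignoring class.

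**5. Does the gain survive a class-respecting analysis?** Simulation with 3 classes of 50 per arm; ratios are adjusted variance over change-score variance.

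| Analysis | Setting | Ratio |
|---|---|---|
| Pupil-level slope, class-level test | rho 0.3 to 0.7, same at both levels | 0.65 to 0.88 |
| Pupil-level slope | pupil 0.5, class 0.9, ICC 0.05 to 0.10 | 1.07 to 1.28, depending on ICC and on how the slope is pooled |
| ANCOVA on six class means | range of settings | about 1.0 to 1.4 |

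The last row is expected. The slope rests on 4 within-arm degrees of freedom, so the variance inflates by about 1 + 1/(4-2) = 1.5. At rho 0.5 this gives 0.75 × 1.5 = 1.13, and 1.12 was simulated at ICC 0.05. Residual degrees of freedom also fall from 4 to 3, and the critical t rises from 2.78 to 3.18. At ICC 0.05 and a true effect of 0.5 SD, power was 0.39 against 0.43 for change at rho 0.5, and 0.50 against 0.62 at rho 0.7.

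**The case against.** The strongest reply is that baseline adjustment is not a free gain in a six-class trial. This stands in part. ANCOVA on class means usually loses. A pupil-level slope can lose too when class means are far more stable over time than pupils within classes. The ratio (1+rho)/2 needs equal SDs and one correlation at both levels. A reader might infer that the change score can never be the more precise choice; step 5 shows that it can.

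A second reply is that the change score is not biased. That is right over repeated random allocation of classes. The error in step 3 is conditional on the imbalance that actually arises. Nor is the imbalance ignored: the change score removes D and overshoots by (1-rho)D.

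Third, the larger values of D exist only because of clustering, which is a separate matter, and both rho and ICC are assumed. This is also true. The precision ratio, however, does not depend on ICC when one rho holds at both levels.

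Fourth, details of covariates may be left to a statistical analysis plan. Here section 3.10 does not leave the method open; it names the tests.

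A reader might also infer that the activity, diet and sleep questionnaires, collected "in order to eliminate metabolic interferences resulting from other factors" (section 3.3), should enter the model as baseline covariates. The protocol does not support this. Section 3.5 does not list them in the testing before instruction, section 3.3 introduces them for the teaching period, and scores taken after allocation may be changed by the curriculum. Metabolites also have their own analysis in section 3.8.

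**Conclusion.** The point holds as a recommendation on the choice of analysis, not as an error that invalidates the trial. For physical and mental indicators with moderate pre-post correlation, the planned t-test on change gives up 15% to 35% of the variance that adjustment would save (rho 0.7 to 0.3). It also leaves a conditional error of about 0.06 to 0.11 SD for a typical chance imbalance at ICC 0.05 and rho 0.7 to 0.5. At rho near 0.9, which is plausible for BMI, the saving is about 5% and hardly matters.

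These sizes assume equal pre and post SDs, the same rho for pupils and classes, and about 50 pupils in each of six classes. They apply to a pupil-level baseline slope inside an analysis that respects class, not to ANCOVA on class means. The baseline significance test adds nothing to either method.

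**What to change.** In section 3.10, replace the independent t-test on change by a regression of the week-12 value on arm, the pupil's own baseline value of the same indicator, and sex (where both sexes take the same test). Estimate the baseline slope at pupil level. Include class as a random effect with a small-sample correction to the degrees of freedom, or compare baseline-adjusted class means by a class-level t-test. State that ANCOVA on the six class means will not be used.

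Report baseline means and SDs by arm without P values. Keep a class-respecting change-score analysis as a sensitivity analysis. Do not add activity, sleep or diet scores to this model.

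The cost is a change of wording, because outcome baselines and sex are already available. The change should be fixed before the arms are compared. The remaining risk is some loss of precision if the class-level correlation is much higher than the pupil-level one; the sensitivity analysis would help to show this.

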3.6 Test Indicators and Methods

The physical health indicators were tested according to the "National Physical Fitness Standards for Students (2014 Revision)," including body shape, cardiorespiratory endurance, speed, strength, flexibility, and muscular endurance. The body composition indicators were assessed using body mass index (BMI) and waist circumference. Cardiorespiratory endurance was tested using vital capacity. Strength was measured by a 1-minute sit-up test (female) or pull-up test (male). Speed was measured using the 50-meter run. Flexibility was tested using the sit-and-reach test. Muscular endurance was measured with an 800-meter run (female) or 1000-meter run (male). The main testing methods are as follows:

1) Body Mass Index (BMI): The participant stands barefoot on a height measuring platform with their back against the column, feet together, and body straight. The participant's heels, sacrum, and scapula should be in contact with the column, with the head aligned horizontally. The height is recorded in centimeters (cm), accurate to one decimal place. Weight is recorded in kilograms (kg), also accurate to one decimal place. BMI is calculated using the formula: BMI = weight / height² (kg/m²).

2) Vital Capacity: A dry, disposable mouthpiece (or disinfected non-disposable mouthpiece) is used. The participant should take a deep breath and exhale into the mouthpiece until no more air can be expelled, avoiding inhalation during the test. The final reading on the LCD screen is recorded as the vital capacity in milliliters (mL), and the maximum value is selected as the result.

3) 1-Minute Sit-Up Test (Female) / Pull-Up Test (Male): For sit-ups, the participant lies on a mat with arms crossed over their chest, palms pressed against the shoulders, and feet flat on the ground, with knees at a 90° angle. Each sit-up is counted when the elbows touch or exceed the knees. The number of sit-ups performed in 30 seconds is recorded. For pull-ups, the participant grasps a horizontal bar with both hands shoulder-width apart, hanging with straight arms. After stabilizing their body, they pull up until the chin is above the bar, and the number of successful pull-ups is recorded.

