3.8 Metabolomics Method

Forty students were randomly selected (20 from the experimental group and 20 from the control group). Urine samples (15 ml) were collected from these students before instruction, after the first session of instruction, and after 12 weeks of instruction. The samples were processed and analyzed using non-targeted metabolomics based on liquid chromatography–mass spectrometry (LC-MS) to identify differential metabolites before and after a single session of instruction, as well as before and after long-term instruction. Metabolic pathway analysis was also conducted to obtain metabolic fingerprints before and after the intervention.

Principal component analysis (PCA) and orthogonal partial least squares discriminant analysis (OPLS-DA) were employed to elucidate the differences in metabolic profiles before and after the intervention. Differential metabolites were further screened using t-tests of intragroup mean metabolite concentrations, OPLS-DA, and clustering analysis. The mass-to-charge ratios (m/z) of the metabolites were matched and analyzed against the Human Metabolome Database and the Kyoto Encyclopedia of Genes and Genomes (KEGG) database for structural identification, enrichment, and topological analysis of the differential metabolites. This approach was used to explore the metabolic pathways involved in the differential metabolites before and after a single session of instruction, as well as before and after long-term instruction, under the Healthy Physical Education Curriculum Model of China.

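### One unadjusted P<0.05 is the only threshold in the protocol: the untargeted metabolite screen has no stated error control, and about 11 health indicators are tested with no primary.

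*Protocol*

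**What the plan says.** Section 3.10 of the protocol sets the threshold for the whole document: "Statistical significance is set at P<0.05". It names the tests too. "Paired sample t-tests will be used to compare differences before and after intervention for each indicator", and independent-sample t-tests compare the groups at baseline and on the pre-to-post change. It mentions no primary outcome, ordering of indicators or multiplicity adjustment, and neither does any other section.

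Section 3.6 describes the physical measures as "including body shape, cardiorespiratory endurance, speed, strength, flexibility, and muscular endurance". These domains are then broken into individual tests, and section 3.7 adds the psychological scales.

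Section 3.8 covers the metabolomics: urine from 20 students per group, untargeted LC-MS, and comparisons across a single lesson and across the 12 weeks. "Differential metabolites were further screened using t-tests of intragroup mean metabolite concentrations", together with OPLS-DA and clustering. The metabolites found are matched to databases and passed to enrichment and topology analysis. No p-value cut-off is stated there.

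The sample-size paragraph (participants and grouping) rests on one two-group comparison with "a medium effect size of 0.5, an α error probability of 0.05, and a power (1 - β error probability) of 0.80", and does not say which indicator it concerns.

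**The concern.** A threshold of 0.05 per test bounds the error of one test. The plan runs it over two large families.

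The first is the untargeted metabolite screen, where the number of tests is open-ended. Chance hits that survive go into the pathway analysis. Since metabolic mechanisms are part of the stated objective, they could be reported as the explanation of how the curriculum works.

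The second is the set of health indicators. With none named as primary, the trial could claim success on whichever one crosses 0.05, although the sample size was worked out as if there were only one.

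**Working it through.** **1. The plan's own figure.** Inputs: d = 0.5, α = 0.05, power 0.80, "with equal sample sizes in both groups". The stated result is "The minimum required sample size for the study was calculated to be 64". The two-sided t calculation gives 63.77, so 64 **per group** (power 0.801), or 128 in total; a one-sided test would need 51 per group. The figure thus reproduces as the per-group size for one two-sided test at 0.05. Whether 64 was meant per group or in total is a separate question. What matters here is that it allows for one test only.

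**2. Number of health indicators** (counted from sections 3.6 and 3.7; the protocol gives no total):
- Physical, 8: BMI, waist circumference, vital capacity, sit-ups or pull-ups, standing long jump, 50 m run, sit-and-reach, 800 m or 1000 m run. Sex-specific pairs count once.
- Psychological, 3: health behaviours, sports ethics, depressive symptoms.
- Total: 8 + 3 = 11.

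**3. Error over the 11 between-group change tests, all nulls true.**
- Expected false positives: 11 × 0.05 = 0.55, whatever the correlation.
- Chance of at least one, if independent: 1 − 0.95^11 = 0.431.
- The indicators are measured on the same children, so correlation is likely. The protocol gives no value. Simulation with an assumed common correlation:

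| Assumed correlation | Chance of at least one false positive |
| --- | --- |
| 0 | 43% |
| 0.3 | 38% |
| 0.5 | 30% |
| 0.8 | 18% |

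- Section 3.10 names more tests than these. With two paired tests (one per group), one baseline test and one change test per indicator, there are 11 × 4 = 44 tests and 44 × 0.05 = 2.2 expected false positives if every null held.

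**4. Metabolites.** The feature count is not given, so the range is an assumption. Expected chance t-test hits per contrast = 0.05 × number of null features:

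| Null features (assumed) | Per contrast | Over two contrasts |
| --- | --- | --- |
| 100 | 5 | 10 |
| 500 | 25 | 50 |
| 1,000 | 50 | 100 |
| 5,000 | 250 | 500 |

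These expected counts do not depend on independence. They are hits on the t-test alone, before OPLS-DA, clustering or database matching, and they assume 0.05 is the cut-off used.

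**5. Would OPLS-DA remove them?** Checked on pure noise: 20 pre and 20 post samples, independent features, 200 runs, with a one-component PLS-DA as a simple stand-in. The two time points separated completely at both 1,000 and 5,000 features. A filter of VIP > 1 (an assumed cut-off; the protocol states none) removed essentially none of the features with paired P<0.05, which averaged about 50 and 250. The filter and the t-test rank features by nearly the same quantity, so the one is not an independent check on the other.

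**The case against.** Five points can fairly be made on the other side.

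*The protocol does not say that P<0.05 governs the metabolites.* This is correct. Section 3.10 speaks of indicators, a word used elsewhere for physical and mental health measures, and section 3.8 has its own analysis text with no cut-off. A reader might infer that the protocol expressly applies 0.05 to every feature. It does not. What stands is that no error control is stated for the screen, and that 0.05 is the only threshold on offer.

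*The 5 to 250 are not reported metabolites.* Also correct. A reader might take them as the number of false metabolites that will be published. The feature count is assumed, and further filters and structural matching come between the t-test and the pathway analysis. None of those steps controls the false-discovery rate, however, and the noise check shows that the multivariate filter may remove very little.

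*Chance findings are not a foregone conclusion on the health side.* It is tempting to say that the design makes a false health claim the expected result, or to quote 43% alone. With 0.55 false positives expected over the 11 change tests, no false positive is the likelier outcome even under independence (57%), and correlation lowers the risk further. Even so, 18% is more than three times the nominal 5%.

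*An unseen SAP might settle this.* A choice between adjustment procedures could well sit there. But section 3.10 already fixes both the tests and a flat threshold, and a sample size for one comparison needs to say which comparison.

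*The metabolomics is exploratory.* That argues for false-discovery control rather than family-wise control. It does not argue for none, given that mechanism is a stated objective.

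**Conclusion.** The concern holds in a limited form. As written, the protocol leaves the metabolite screen without stated error control, and tests about 11 health indicators at an unadjusted 0.05 with no primary.

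It is firmest for the metabolites: 5 to 250 chance t-test hits per contrast, conditional on 100 to 5,000 null features and on 0.05 being the cut-off. For the health indicators, the family-wise error of the change tests is about 18% to 43%, conditional on the global null, a count of 11 and assumed correlations between 0.8 and 0. These figures also treat students as independent, although allocation is by class. The documents do not support saying that false results are certain. They do show that a significant result under this plan would not carry the 5% error rate it implies.

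**What to change.** **Section 3.8.** Call a metabolite differential only at Benjamini-Hochberg q<0.05 within each contrast, and pass only those to the pathway analysis. Interpret an OPLS-DA model only if its cross-validated Q2 passes a permutation test.

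**Section 3.10.** Name one primary indicator, tested between groups on change at 0.05, and tie the sample size to it. Test the other ten by Holm at 0.05 only if the primary is significant; otherwise report them as exploratory. The gate matters. A primary at 0.05 plus an ungated Holm at 0.05 on the rest can bring the family-wise error near 10% (1 − 0.95² = 0.0975 if the two parts are independent). Holm across all 11 is an acceptable alternative.

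**Cost.** The change takes a few sentences and standard software, and no new data. There will be fewer significant results. With a gated primary, the primary keeps its full 0.05. If Holm spans all 11, the strictest step is 0.05/11 = 0.00455. At d = 0.5 that needs 111 per group for 80% power. Power would be 0.48 with 64 per group and 0.93 with 150 per group, which is half of the planned enrolment ("involving six classes (approximately 300 students) who voluntarily participated"). These power figures ignore clustering by class. The loss will be felt most in the metabolomics, with 20 students per group.

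False-discovery control does not make a within-group change attributable to the curriculum. Real changes due to time, diet or growth would still pass it.
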